1. If a subject discontinues treatment early but does not withdraw from the study, the EOT visit and subsequent follow-up visits should be completed as far as possible. For subjects who withdraw early from the study, an early withdrawal visit will be completed. The required procedures, examinations, and assessments will be the same as those conducted at the EOS visit. The sample collection time or safety examination time should be close to the time of withdrawal from the study as far as possible. At the "early withdrawal" visit, procedures, examinations and assessments will be waived if there are results within 3 days.
2. For demographics, the age, sex, ethnicity, smoking history, alcohol consumption and menstrual history of the subjects should be recorded.
3. Medical, medication and surgical history: ① History of SLE: The date of diagnosis of SLE should be recorded. ② SLE medication history: The medication use (including specific drugs/treatment, dosage, and usage, etc.) for at least 2 years prior to the screening visit should be recorded. ③ Medical

history of other diseases: The occurrence of other diseases (including disease name and time of onset, etc.) within at least 6 months prior to the screening visit should be recorded. ④ Previous treatment history of other diseases: The treatment (including specific drugs/treatment, usage and dosage, etc.) within at least 1 month prior to the screening visit should be recorded. ⑤ Previous surgical history: The surgery (including name and date of surgery, etc.) within at least 6 months prior to the screening visit should be recorded.

4. Body height/weight: Body height (cm) and weight (kg) will be measured at screening (D-28 to D-1), and BMI will be calculated based on body height and weight. Only weight will be measured at V2, V6, V7, V8, V9, V12, EOT visit, and EOS visit.

5. Infectious disease screening:

a) Hepatitis B screening: Hepatitis B five items (hepatitis B virus surface antigen [HBsAg], hepatitis B virus surface antibody [HBsAb], hepatitis B virus core antibody [HBcAb], hepatitis B virus e antigen [HBeAg] and hepatitis B virus e antibody [HBeAb]); hepatitis B virus deoxyribonucleic acid (HBV-DNA) test may be added if necessary. HbsAg-positive subjects as well as subjects with both HbcAb-positive and HBV-DNA-positive results need to be excluded from the study;

b) Hepatitis C screening: Hepatitis C virus (HCV) antibody, and HCV-ribonucleic acid (HCV-RNA) test may be added if necessary;

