14. Blood chemistry: including glucose, total cholesterol, low density lipoprotein cholesterol, high density lipoprotein cholesterol, alanine aminotransferase, aspartate aminotransferase, total protein, albumin, total bilirubin, direct bilirubin, lactate dehydrogenase, alkaline phosphatase, glutamyl transpeptidase, creatinine, urea/urea nitrogen, uric acid, sodium, potassium, chloride, calcium. Serum chemistry results within 3 days prior to the first dose will be acceptable at the baseline visit.

15. Coagulation: including prothrombin time, activated partial thromboplastin time, thrombin time, fibrinogen and international normalized ratio. Coagulation results within 3 days prior to the first dose will be acceptable at the baseline visit.
16. Urinalysis: including urine protein, glucose, ketones, occult blood, microscopic examination (including red blood cells/high power field, white blood cells/high power field, poikilocytes, casts and specific classification), urobilinogen, urine bilirubin, nitrite, urine specific gravity, and acidity or alkalinity. Urinalysis results within 3 days prior to the first dose will be acceptable at the baseline visit. If the subject is menstruating, the urinalysis may be postponed until after the menstrual period.
17. Pregnancy test: for women of childbearing potential only. Blood pregnancy tests will be performed at the screening visit and the EOS visit, while blood or urine pregnancy tests will be performed at other visits. Unscheduled blood or urine pregnancy tests may be performed at the investigator's discretion during the course of the study.
18. 24-hour urine protein will only be conducted for subjects whose urine protein/creatinine ratio exceeds the ULN during the screening period. The 24-hour urine protein and urine protein/creatinine ratio at the baseline visit can be completed on D1 or within 48 hours before D1. The 24-hour urine protein and urine protein/creatinine ratio within 3 days prior to the first dose are acceptable at the baseline visit.
19. Immunology-related endpoints: including IgG, IgA, IgM, IgE, complement (C3, C4), and anti-ds-DNA antibody. These will be tested by the laboratories of each study site during the screening period. Baseline and subsequent examinations will be conducted by the central laboratory. Among them, the results of IgG, IgA, IgM, and IgE at baseline and thereafter will not be provided to each study site before unblinding to avoid breaking of blindness.

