To date, there are no confirmed important risks for CM313. Based on the safety information of similar products already on the market, IRR, neutropenia/thrombocytopenia, interference with indirect antiglobulin test (IAT), and hepatitis B virus reactivation are listed as potential important risks of CM313.

As of 11 Jan 2022, the clinical trial data of CM313MM001 are as follows: 1) Safety: No DLT events have occurred so far. TEAEs occurred in 9/10 subjects and TRAEs occurred in 7/10 subjects, but the vast majority of TEAEs and all TRAEs were Grade 1 or 2. All Grade 3 TEAEs were judged to be unrelated to the IMP; 2) Efficacy: The best efficacy evaluation results of the

3 subjects in the 2 mg/kg dose level were VGPR, MR, and SD, respectively; while the neoplasm evaluation results of the 2 subjects in the 4 mg/kg dose level who had completed the first efficacy evaluation were SD and VGPR, respectively. The above findings indicate that CM313 has good safety and tolerability in patients with relapsed/refractory MM and lymphoma, and has shown preliminary efficacy.

Based on the mechanism of action of CM313, pharmacology findings, and preliminary efficacy findings, CM313 is expected to have potential benefits for the treatment of active SLE. Based on the available safety findings of CM313 and the safety data of the marketed product with the same target, daratumumab injection, CM313 has good safety and tolerability. Therefore, it can be considered that the overall benefits of CM313 outweigh the risks.

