### **3.7.2. Exclusion Criteria**

A subject will not be eligible for inclusion in this study if any of the following criteria apply:

1. Renal disorder: Severe lupus nephritis (defined as urine protein  $> 6$  g/24 hours or serum creatinine  $> 2.5$  mg/dL or  $221 \mu\text{mol/L}$ ) within 8 weeks before the first dose of IMP, or active nephritis requiring treatment with drugs prohibited by the protocol, or conditions requiring hemodialysis, or treatment with prednisone  $\geq 100$  mg/d or equivalent glucocorticoids for  $\geq 14$  days;
2. Subjects with central nervous system diseases caused by SLE or non-SLE (including epilepsy, psychosis, organic encephalopathy syndrome, cerebrovascular accident, encephalitis, central nervous system vasculitis) within 8 weeks before the first dose of IMP;
3. The presence of the following laboratory test abnormalities, including but not limited to:
  - a) Subjects with abnormal hepatic function, such as aspartate aminotransferase (AST) or alanine aminotransferase (ALT)  $> 2$  times the upper limit of normal (ULN), total bilirubin  $> 1.5$  times ULN, or

- b) Subjects with abnormal renal function: creatinine (Cr) or urea nitrogen (BUN) > 1.5 times ULN; screening glomerular filtration rate (eGFR)  $\leq 60$  mL/min/1.73 m^2, or
  - c) Subjects with abnormal hematology results: white blood cell count <  $2.5 \times 10^9$ /L, hemoglobin < 85 g/L, platelet count <  $50 \times 10^9$ /L;
4. Subjects with a history of clinically significant diseases that the investigator believes will pose a risk to the subject's safety, or that will affect the safety or efficacy analysis and evaluation if the disease/condition worsens during the study (such as abnormalities of the circulatory system and endocrine system, nervous system diseases, blood system diseases, immune system disorders, mental illness, and unstable metabolic abnormalities), for example: 1) cardiovascular disorder: history of acute myocardial infarction, or unstable angina pectoris, severe arrhythmia (multifocal premature ventricular contractions, ventricular tachycardia, ventricular fibrillation) within 6 months before screening; New York Heart Association (NYHA) Class III-IV; 2) subjects with known moderate or severe persistent asthma within 5 years before screening, or subjects with ongoing inadequately controlled asthma;

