  5. Subjects who may have active mycobacterial infection, defined as: chest X-ray (posterioranterior and lateral position) examination suggests active tuberculosis infection within 3 months prior to screening/during the screening period (if required by the ethics, tuberculosis testing will be performed according to site procedures);
  6. Subjects with active hepatitis, positive hepatitis B surface antigen (HBsAg), positive hepatitis B core antibody (HBcAb) + positive hepatitis B virus (HBV) deoxyribonucleic acid (DNA), or positive hepatitis C virus (HCV) antibody at screening;
  7. A history of human immunodeficiency virus (HIV) infection, or HIV antibody positive at screening;
  8. Subjects with treponema pallidum antibody positive at screening;
  9. Having chronic active infection or acute infection requiring systemic treatment with antibiotics, antivirals, antiparasites, antiprotozoals or antifungals within 4 weeks prior to screening, or having superficial skin infections requiring treatment within 1 week prior to screening. Note: After the infection is cured, the patient may be re-screened once;
  10. Subjects with known or suspected history of immunosuppression, including history of invasive opportunistic infections (e.g., histoplasmosis, listeriosis, coccidioidomycosis, pneumocystosis, and aspergillosis), even if the infection has recovered; or have unusual frequent, recurrent, or prolonged infections (as judged by the investigator);

11. Major surgery (craniotomy, thoracotomy, or laparotomy) or unhealed wounds, ulcers, or fractures within 4 weeks prior to the first dose of IMP, or major surgery planned during the study;
12. Subjects with malignancy within 5 years prior to screening (except for completely cured cervical carcinoma in situ and non-metastatic squamous cell or basal cell carcinoma of the skin);
13. A history of major organ transplant (e.g., heart, lung, kidney, liver) or hematopoietic stem cell/or bone marrow transplant;
14. Subjects who received live or live attenuated vaccines within 4 weeks prior to the first dose of IMP or plan to receive the above during the study;
15. Subjects who have participated in any clinical trial within 4 weeks before the first dose of IMP or who are within 5 half-lives of the investigational product in the previous clinical trial (whichever is longer);

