## 4. Study Procedures

### 4.1. Study Steps

#### 4.1.1. V1 (D-28 to D-1, Screening Period)

Subjects who sign the ICF should complete protocol-specified screening tests/assessments within 28 days prior to the first dose to determine their eligibility for enrollment.

Subjects will maintain a stable standard of care regimen for at least 30 days before the first dose of IMP. A stable standard of care regimen refers to the stable use of any of the following (alone or in combination): corticosteroids, antimalarials, NSAIDs, immunosuppressive or immunomodulatory agents, such as azathioprine, mycophenolate (including mycophenolate mofetil, mycophenolic sodium), methotrexate, leflunomide, tacrolimus, ciclosporin. [Note: Routine dose reduction of corticosteroids  $\leq 20$  mg/d prednisone (or equivalent dose of other corticosteroids) is also considered stable treatment]

All study procedures to be completed at screening are as follows:

- Obtain informed consent and sign ICF;
- Confirm eligibility according to inclusion/exclusion criteria;
- Collect demographic data: including age, sex, ethnicity, smoking history, alcohol consumption history, and menstrual history;
- Collect medical history, medication history, and surgical history: ① History of SLE: The date of SLE diagnosis should be recorded. ② SLE medication history: The medication use (including specific drugs/treatment, dosage, and usage, etc.) for at least 2 years prior to the screening visit should be recorded. ③ Medical history of other diseases: The occurrence of other diseases (including disease name and time of onset, etc.) within at least 6 months prior to the screening visit should be recorded. ④ Previous treatment history of other diseases: The treatment (including specific drugs/treatment, usage and dosage, etc.) within at least 1 month prior to the screening visit should be recorded. ⑤ Previous surgical history: The surgery (including name and date of surgery, etc.) within at least 6 months prior to the screening visit should be recorded.
- Measure body height and weight, and calculate body mass index (BMI);
- Perform infectious disease screening, including hepatitis b screening: hepatitis B five items (HBsAg, HBsAb, HBcAb, HBeAg, and HBeAb), and HBV-DNA if necessary; perform hepatitis c screening: HCV antibody, and HCV-RNA if necessary; HIV

- screening: HIV antibody; syphilis screening: treponema pallidum antibody;

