## **5. Methods of Assessment**

### **5.1. Routine Assessments**

Demographic data: The subjects' age, sex, ethnicity, smoking history, alcohol consumption history and menstrual history will be inquired and recorded at screening.

Medical, surgical and medication history: ① History of SLE: The date of SLE diagnosis will be recorded. ② SLE medication history: The medication use (including specific drugs/treatment, dosage, and usage, etc.) for at least 2 years prior to the screening visit should be recorded. ③ Medical history of other diseases: The occurrence of other diseases (including disease name and time of onset, etc.) within at least 6 months prior to the screening visit should be recorded. ④ Previous treatment history of other diseases: The treatment (including specific drugs/treatment, usage and dosage, etc.) within at least 1 month prior to the screening visit should be recorded. ⑤ Previous surgical history: The surgery (including name and date of surgery, etc.) within at least 6 months prior to the screening visit should be recorded.

Body height, weight, BMI: Body height (cm) and weight (kg) will be measured during the screening period V1 (D-28 to D-1), and BMI will be calculated based on body height and weight. Only weight will be measured at visits V2, V6, V7, V8, V9, EOT, V12, and EOS.

Infectious disease screening: This will be conducted during the screening period V1 (D-28 to D-1) and includes: hepatitis B screening: hepatitis B five items (HBsAg, HBeAg, HBsAb, HBcAb, HBeAb, and HBV-DNA if necessary); hepatitis C screening: HCV antibody (HCV-RNA if necessary); HIV screening: HIV antibody; tuberculosis screening: chest X-ray (posteroanterior and lateral position), additional tuberculosis screening-related tests may be added according to the study site's diagnostic and treatment routine; syphilis screening: syphilis spirochete antibody.

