#### **5.2.4. Laboratory Tests**

Laboratory tests include hematology, blood chemistry, urinalysis, and coagulation function. See Section 3.9.1 for specific details. It will be conducted at V1 (screening visit), V2 (baseline visit), V3, V4, V5, V6, V7, V8, V9, V10 (EOT visit), V11, V12, V13, and V14 (EOS visit).

During the course of the study, the frequency of clinical laboratory tests may be increased if the investigator deems that it is necessary for safety considerations. Abnormal laboratory results judged by the investigator to be clinically significant should be reported as AEs.

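### Hepatitis B reactivation is a named potential risk and HBcAb-positive, HBV-DNA-negative subjects may enter, yet none of the 12 post-dose visits has a scheduled HBV-specific test

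*Protocol*

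**What the plan says.** **The risk.** Section 3.4 says that "IRR, neutropenia/thrombocytopenia, interference with indirect antiglobulin test (IAT), and hepatitis B virus reactivation are listed as potential important risks of CM313". It draws the list from similar products already on the market and says that CM313 itself has no confirmed important risk so far.

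**Entry.** Criterion 6 in Section 3.7.2 excludes active hepatitis, HBsAg positivity, and the combination "positive hepatitis B core antibody (HBcAb) + positive hepatitis B virus (HBV) deoxyribonucleic acid (DNA"). Note 5a to Table 1 repeats the rule: "HbsAg-positive subjects as well as subjects with both HbcAb-positive and HBV-DNA-positive results need to be excluded from the study". Criterion 3a adds a liver-function limit, beginning "Subjects with abnormal hepatic function, such as aspartate aminotransferase (AST) or alanine aminotransferase (ALT"), set at more than 2 times ULN.

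**HBV testing.** Section 5.1 gives the timing: "Infectious disease screening: This will be conducted during the screening period V1 (D-28 to D-1"). Section 4.1.1 gives the content: "hepatitis B five items (HBsAg, HBsAb, HBcAb, HBeAg, and HBeAb), and HBV-DNA if necessary". In Table 1 the infectious disease row is marked under V1 only. The procedure lists for V3 to V14 (Sections 4.1.2.2 to 4.1.3.2) and Section 5.2.4 contain no HBV serology or HBV-DNA.

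**What is measured after dosing.** Blood chemistry is marked at every visit, and Note 14 includes "alanine aminotransferase, aspartate aminotransferase, total protein, albumin, total bilirubin, direct bilirubin". Section 5.2.4 adds that "the frequency of clinical laboratory tests may be increased if the investigator deems that it is necessary for safety considerations". Section 4.4 allows unscheduled visits, with re-examination of clinically significant abnormalities.

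**The concern.** The exclusion rule leaves in the trial a group for whom the named risk is relevant: subjects with a positive core antibody and no detectable virus at entry. For them the protocol does nothing HBV-specific once dosing starts. A site that followed the plan exactly would never run a scheduled post-dose HBV test in these subjects.

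Safety is the primary objective. Section 3.1 makes entry to the four weekly doses depend on the investigator finding safety and tolerability acceptable after the 28-day single-dose phase, and the same D1 to D28 data inform dose escalation. For HBcAb-positive subjects that judgement contains no post-dose HBV result.

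Liver chemistry does not name its cause, and the protocol itself supplies other explanations for a raised transaminase. AST increase was a treatment-related event in 1 of 10 subjects in study CM313MM001 (Section 1.3.2), and lupus hepatitis is item 62 of the BILAG-2004 scale (Appendix 4). Nothing in the text directs the investigator from an abnormal panel to an HBV test.

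**Working it through.** The plan states no figure on this point, so the check is a count from the schedule and a side-by-side reading of the rules.

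**1. Who can enter.** Criterion 6 and Note 5a, read together, for subjects without active hepatitis:

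| HBsAg | HBcAb | HBV-DNA | Outcome |
|---|---|---|---|
| positive | any | any | excluded |
| negative | positive | positive | excluded |
| negative | positive | negative | may enter |
| negative | positive | not done | rule cannot be applied |

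The last row arises because HBV-DNA is done at screening only if judged necessary (Note 5a, Sections 4.1.1 and 5.1), although the rule for HBcAb-positive subjects turns on it.

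**2. Scheduled tests after the first dose.** The first dose is at V2 (D1), so the post-dose visits are V3 to V14: 14 − 2 = 12.
- HBV-specific tests scheduled: 0 of 12.
- Panels with ALT, AST and bilirubin: 12 of 12. Eight are weekly (D8, 15, 22, 29, 36, 43, 50, 57) and four follow at 14-day intervals (D71, 85, 99, 113).

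**3. What is known before the D29 dose.** Available: screening serology, HBV-DNA if it was done, and liver panels from V3, V4 and V5. Not available: any scheduled HBV result obtained after exposure.

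**4. Spacing of a feasible HBV-DNA schedule** (pre-D29, V10 at D57, V12 at D85, V14 at D113):
- First draw at V6 (D29): 29 − 1 = 28; 57 − 29 = 28; 85 − 57 = 28; 113 − 85 = 28 days.
- First draw at V5 (D22), so that the result is back before the D29 dose: 22 − 1 = 21; 57 − 22 = 35; then 28 and 28 days.

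The interval is therefore 21 to 35 days, or 3 to 5 weeks, depending on the first draw.

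**5. Assays.** Four per HBcAb-positive subject. If every planned subject were HBcAb-positive, the ceiling is 4 × 40 = 160, or 4 × 30 = 120 if the optional 16 mg/kg level is not run.

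**6. How many subjects.** The documents give no HBcAb-positive share. As an assumption only, let the share p among the 8 × 4 = 32 CM313 subjects be 5% to 30%. The expected number is 32p and the chance of at least one is 1 − (1 − p)^32:
- p = 5%: 1.6 expected; 81%
- p = 10%: 3.2 expected; 97%
- p = 20%: 6.4 expected; over 99.9%
- p = 30%: 9.6 expected; over 99.9%

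These are chances of enrolling such a subject. They say nothing about the chance of reactivation, for which the documents give no rate.

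**The case against.** The best defence is that this is a choice of monitoring intensity and that the safety net is dense. The risk is class-derived and unconfirmed for CM313, and Section 3.4 promises no HBV-specific monitoring, so the schedule contradicts nothing. Liver panels run weekly to D57 and every 14 days after that, and physical examination is done at every visit. Section 4.4 permits unscheduled re-examination. Section 3.8.7 requires IMP to be stopped for a disease that precludes continuing, Section 3.8.6 suspends the study for any IMP-related SAE, and criterion 24 lets the investigator decline a subject. All of this stands, and it limits the weight of the point. It does not close the gap: none of these provisions names HBV, and Section 5.2.4 speaks of the frequency of clinical laboratory tests, which that section defines as hematology, chemistry, urinalysis and coagulation.

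A reader might infer more than the documents support, in four ways:
- *That reactivation would be recognised late.* The documents give no lag between viraemia and liver injury, and HBV-DNA every 3 to 5 weeks is less frequent than the existing panels. It cannot be shown from the text that it would flag the event sooner; what it adds is specificity.
- *That the D29 decision is made with no HBV information.* Screening serology exists. What is missing is a post-dose result.
- *That HBV would be looked for only after a liver rise.* Section 4.4 lets the investigator act on the subject's overall condition.
- *That HBV stands alone among the four named risks.* The contrast is uneven: the IAT is also tested only at screening, and its follow-through is an identification card (Note 7).

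**Conclusion.** The point holds as a gap in scheduled safety monitoring. The risk is named, subjects for whom it is relevant may enter, and the number of scheduled post-dose HBV-specific tests is 0 at 12 visits, against 12 liver panels. Detection therefore depends on non-specific signals and investigator discretion, and the D29 decision lacks a post-dose HBV result in HBcAb-positive subjects. It is not an absence of any signal, and the documents do not show that recognition would be delayed.

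The size in subjects is unknown, because neither the HBcAb-positive share nor a reactivation rate is given. The conclusion rests on the schedule as printed. The protocol refers to no separate manual for HBV monitoring, and a visit schedule is protocol content rather than a matter for the analysis plan. The change is worth making because it is targeted and cheap, not because harm has been demonstrated.

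**What to change.** **Schedule.** Add a Table 1 row for HBV-DNA in HBcAb-positive subjects only, at existing visits: for example before the D29 dose (drawn at V5 or V6, whichever lets the result be back before dosing), then V10, V12 and V14 or early withdrawal. The exact visits are the sponsor's choice.

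**Action.** State that newly detectable HBV-DNA leads to holding IMP under Section 4.2, recording an AE, referral for antiviral assessment, and follow-up under Section 6.1.2. Section 4.2 already requires discussion with the sponsor's medical monitor before dosing resumes. In this example only the first test can change dosing, because the last dose is at D50; the other three serve safety follow-up.

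**Screening.** In Note 5a and Sections 4.1.1 and 5.1, require HBV-DNA for every HBcAb-positive subject, since criterion 6 cannot be applied without it, and keep the discretionary wording for all others. This makes a test mandatory for one group, so it is a substantive change and should be presented as one.

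**Cost.** About four post-dose assays per HBcAb-positive subject, with an arithmetic ceiling of 160 for 40 subjects; the actual number is not in the documents. A screening assay is added wherever it would not have been done. No visits are added, since blood is already drawn at each of these. A protocol amendment is needed and, under Section 11.7, possibly a revised consent form and re-consent.
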